# Assessing the link between implementation fidelity and health outcomes for a trial of intensive case management by community health workers: a mixed methods study protocol

**DOI:** 10.1186/s12913-017-2320-2

**Published:** 2017-07-17

**Keywords:** Implementation fidelity, Primary health care, Chronic disease, Indigenous

## Abstract

**Background:**

Better systems of care are required to address chronic disease in Indigenous people to ensure they can access all their care needs. Health research has produced evidence about effective models of care and chronic disease strategies to address Indigenous health, however the transfer of research findings into routine clinical practice has proven challenging. Complex interventions, such as those related to chronic disease, have many components that are often poorly implemented and hence rarely achieve implementation fidelity. Implementation fidelity is “the degree to which programs are implemented as intended by the program developer”. Knowing if an intervention was implemented as planned is fundamental to knowing what has contributed to the success of an intervention.

**Methods:**

The aim of this study is to adapt the implementation fidelity framework developed by Keith et al. and apply it to the intervention implemented in phase 1 of the Getting Better at Chronic Care in North Queensland study. The objectives are to quantify the level of implementation fidelity achieved during phase 1 of the study, measure the association between implementation fidelity and health outcomes and to explore the features of the primary health care system that contributed to improved health outcomes. A convergent parallel mixed methods study design will be used to develop a process for assessing implementation fidelity. Information collected via a questionnaire and routine data generated during phase 1 of the study will be used to explain the context for the intervention in each site and develop an implementation fidelity score for each component of the intervention. A weighting will be applied to each component of the intervention to calculate the overall implementation score for each participating community. Statistical analysis will assess the level of association between implementation fidelity scores and health outcomes.

**Discussion:**

Health services research seeks to find solutions to social and technical problems to improve health outcomes. The development of a tool and methodology for assessing implementation fidelity in the Indigenous primary health care context will help address some of the barriers to the translation of research into practice.

**Trial registration:**

ACTRN12610000812099: 29.9.2010

## Background

Chronic disease is a major contributor to the health differentials in Indigenous populations. This is evident in Australia where the health status of Aboriginal and Torres Strait Islander people sits at the bottom of the league table of first world nations, with chronic disease the biggest contributor to burden of illness [1]. In rural and remote areas of Australia the hospitalisation rates and prevalence of risk factors of chronic disease for Aboriginal and Torres Strait Islander populations is higher than non-indigenous people [2]. It is widely recognized that better systems of care are required to address chronic disease and ensure that Aboriginal and Torres Strait Islander people have access to the care they need [3, 4].

Implementation of effective health service interventions to improve chronic disease outcomes in Aboriginal and Torres Strait Islander populations is complex. Factors that contribute to chronic illness relate to the characteristics of Indigenous populations, infrastructure in Indigenous communities and the capacity of health services to respond to Indigenous health issues. Characteristics of Indigenous populations that contribute to poor health outcomes include the social determinants of health, environmental factors and intergenerational grief and trauma caused by colonisation and racism [5]. Compared with urban areas, there is less access to comprehensive primary health care services in rural and remote locations and greater challenges with accessing specialist care [6, 7]. Workforce supply, skills and capacity to respond to health needs in a culturally competent manner, poor orientation, inappropriate service delivery models, lack of knowledge of chronic disease care guidelines, poor access to information technology and lack of resources are all barriers to effective chronic disease interventions in Indigenous Aboriginal and Torres Strait Islander populations [8–10].

Indigenous health research has produced evidence about effective models of care and chronic disease strategies that address barriers to health improvement [11–13], however the transfer of research findings from trials into routine clinical practice has proven challenging [14, 15]. Campbell et al. suggested that a solution to this problem is to strengthen research design and execution by improved theory development, modelling using qualitative and quantitative methods and evaluating long term implementation [16]. It has been suggested that poor implementation may be due to the characteristics of the intervention itself, the target setting, the research design and the interaction between these elements [15]. Another reason for poor transferability of research into practice is that research reports do not describe the intervention well enough to enable application or authentic replication in the real world setting [17]. A review of 80 studies published in the journal Evidence Based Medicine found that only 39% of non-drug trials adequately described interventions to enable replication [18]. More robust theory development and better description of interventions contribute to improved understanding of intervention components, but they do not help measure if the intervention is being implemented as intended. Therefore additional strategies are needed to monitor the implementation of interventions in a primary health care setting.

Knowing if an intervention was implemented as planned is fundamental to knowing what has contributed to the success of an intervention [19]. Complex interventions, such as those related to chronic disease, have many components that are often poorly implemented and hence rarely achieve implementation fidelity. Implementation fidelity is “the degree to which programs are implemented as intended by the program developer” [20, 21]. Breitenstein et al. state that fidelity is critical to the systematic implementation of evidence based practice [21]. Therefore health service evaluation models need to include measures that assess implementation fidelity.

The RE-AIM framework provides a model for evaluating public health initiatives by scoring the impact of an initiative in a real world setting. The dimensions measured to obtain the score include: reach, efficacy, adoption, implementation and maintenance. These dimensions are evaluated at an individual, organisational and/or community level [14]. While this model is useful for evaluating the effectiveness of chronic disease interventions in real world settings [22, 23], implementation fidelity is not being measured.

In comparison, Carroll et al. developed a conceptual model to measure implementation fidelity by allocating a score for implementation based on adherence to the intervention. The theory underpinning the model is that “implementation fidelity is the moderator between interventions and their intended outcomes” [20]. A score for implementation fidelity is arrived at by measuring adherence to an intervention which can then be correlated to health outcomes. The conceptual model provides a mechanism for assessing the effectiveness of individual components to help identify what is essential to implementing an intervention. Dimensions evaluated include: coverage, frequency and duration.

Carroll et al’s model was adapted and applied by Keith and colleagues to measure implementation fidelity of a nurse lead case management intervention for patients with cardiovascular disease [24]. Using this approach researchers and service managers were able to understand the level of implementation fidelity achieved and the impact of different components of the model on health outcomes. A key addition made by Keith et al. was the inclusion of information about context to help explain the score awarded. Implementation of any new intervention requires active change management and context plays an important role in how an intervention is received and implemented. A predictor of successful change is that the intervention proposed is consistent with the values of the organisation and there is capacity in the organisation to manage change [25]. If the innovation being proposed does not fit with the values of the organisation or is not communicated to those expected to implement it, no matter how effective the intervention may be in research conditions, it is unlikely to be implemented as planned. Measuring implementation fidelity and analysing results using a theoretical lens of change management would assist managers to improve service planning for complex chronic disease interventions and better manage the risks with implementation of chronic disease interventions in Aboriginal and Torres Strait Islander communities.

## Methods/design

The aim of this study is to adapt the implementation fidelity framework developed by Keith et al. and apply it to the communities that participated in phase 1 of the Getting Better at Chronic Care in North Queensland (GBACC) study. The GBACC study was a cluster randomised control trial (RCT)of intensive case management by Indigenous Health Workers of people with complex chronic disease care needs [26]. The primary outcome measure was reduction in HbA1c over 18 month and there were a range of secondary measures including improvement in clinical process measures and hospital avoidance for ambulatory sensitive chronic conditions. The study produced modest results and a possible reason for this is implementation failure of the intervention. This study will quantify the level of implementation fidelity achieved during phase 1 of the GBACC study and investigate the features of the primary health care system that contributed to successful improvement in clinical measures and hospital avoidance for ambulatory sensitive conditions.

The objectives of the study are to:Investigate the features of primary health care service models that contribute to intervention effectiveness for chronic disease care of Indigenous patients and identify if they are present in the context of health services participating in the GBACC study.Assess the level of implementation fidelity achieved for each component of the intervention in each community.Measure the level of implementation fidelity achieved in each communityDetermine if there is any association between implementation fidelity and health outcomes as measured by HbA1c and preventable hospitalisation for diabetes related conditions for communities in the GBACC study.

The study has approval from the Far North Queensland Human Resource Ethics Committee (HREC), University of Queensland HREC and the University of South Australia HREC.

A convergent parallel mixed methods design will be used to develop the measures for assessing implementation fidelity for each component of the intervention implemented during phase 1 of the study. The study will be executed in three stages using a model adapted from Carrol (2007 and Keith (2010). The analysis will use routine data generated by the GBACC study, clinical data collected to measure the outcome from the RCT and additional information collected via a questionnaire to describe the health service context in which the study occurred. The model is illustrated in Fig. 1.

**Fig. 1 Fig1:**
[figure not shown]
Model for assessing Implementation fidelity of GBACC model. *(Adapted from Carroll (2007) and Keith (2010))*

### Stage 1 – Development of tools to describe context and measure implementation fidelity

The stage 1 objective is to develop tools to collect information that explains the service delivery in the intervention sites and confirm the measures to be used to assess implementation fidelity.

#### Development of measures for implementation fidelity

The GBACC model of care (the intervention), the theory underpinning the model and each component of the model was documented during phase 3 of the GBACC study. The description of the model and the measures for assessing each component and the data sources proposed to assess implementation of each component were discussed with stakeholders at a workshop in May 2015. Modifications were made to the description of the component and consensus achieved on measures to be used to assess implementation fidelity of the GBACC study.

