#### Service context questionnaire

The service context questionnaire, stakeholder information sheet and a consent form will be emailed to the Primary Health Care Manager or equivalent in the intervention sites (*n* = 6) to complete. A follow up interview will be conducted the health service managers to explore any missing information and confirm the responses to the questionnaire. The completed questionnaires will be transcribed, collated and coded using nVivo.

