#### Scoring model components

A directed acyclic graph (Fig. 2) illustrates the measures proposed to assess implementation fidelity and map to the dimensions of adherence, dose, quality, and responsiveness. Some measures will be dichotomous (i.e yes or no) while others will be assigned a percentage score based on the level of implementation that occurred. Per protocol analysis will be followed when determining compliance. A weighting for each element will be assigned to reflect the importance of the element. It is expected that additional criteria will need to be developed to define compliance. A workshop will be held with key stakeholders to validate the scoring process and agree on weightings that should be applied to different model components, for each dimension.

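### The yardstick for phase 1 fidelity was written in phase 3 and modified in May 2015, with no stated check against the phase 1 specification

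*Protocol article*

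**What the plan says.** The Background of the protocol article adopts the definition of implementation fidelity as "the degree to which programs are implemented as intended by the program developer". Methods/design fixes the period to which it applies: "This study will quantify the level of implementation fidelity achieved during phase 1 of the GBACC study".

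The section on development of measures says where the reference comes from. The model of care, its theory and "each component of the model was documented during phase 3 of the GBACC study". The description, the measures and the proposed data sources "were discussed with stakeholders at a workshop in May 2015". The outcome was: "Modifications were made to the description of the component and consensus achieved on measures to be used to assess implementation fidelity".

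The section on scoring model components shows that the yardstick is not yet complete: "It is expected that additional criteria will need to be developed to define compliance". A further stakeholder workshop is to validate the scoring and agree the weights. The same section says that compliance will be judged on a per-protocol basis, without saying which protocol.

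Context is collected separately. The service context questionnaire "will be emailed to the Primary Health Care Manager or equivalent in the intervention sites", six in number, and is followed by an interview to fill gaps and confirm answers.

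**The concern.** A fidelity score is a comparison of what was delivered with what was meant to be delivered. On the article's own definition, the second term must be the model intended for phase 1. The stated reference is a description written in a later phase and then altered. If the alteration changed substance, a site could lose marks for something not asked of it in phase 1, or gain marks because the wording had moved towards practice.

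The scores are the independent variable in Stage 3 and the direct answer to the objectives on the level of fidelity. A score that partly records rewording would be read as implementation failure or success. That matters here because Methods/design already describes the trial's results as modest and offers implementation failure as a possible reason.

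A lesser issue concerns context. Answers given years later by someone who was not in post during phase 1 would be a weaker account of why a site scored as it did.

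**Working it through.** The article states no figure on this point, so there is none to reproduce. The check is a comparison of the statements.

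**1. Order of events.**
- Trial registered: 29 September 2010 (Trial registration).
- Intervention delivered in phase 1, which is the period to be scored (Methods/design).
- Model, theory and components documented in phase 3 (Development of measures). The article gives no calendar dates for the phases; that phase 3 follows phase 1 is read from the numbering.
- Description modified and measures agreed in connection with the May 2015 workshop (same section).
- Compliance criteria, weights, questionnaire and scoring still to come, in the future tense (Stages 1 and 2).

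**2. Required reference against stated reference.** The definition requires the developer's intention, applied to phase 1. The stated reference is the phase 3 description as modified in 2015. These are the same only if the later text reproduces the earlier specification. The article does not say that it does, or that the two were compared, although Methods/design cites a source for the trial.

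**3. Does the per-protocol wording close the gap?** It could, if it means the phase 1 trial protocol. It could equally mean the agreed model description. The expectation that further criteria are needed to define compliance suggests that no existing document settles the matter fully.

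**4. What a later change could do to the score.** Assume that a community's score is a weighted mean of its component scores; the article says only that components are weighted and aggregated. Let *p* be the share of total weight carried by items added or modified after phase 1, *F_T* the community's mean score on those items and *F_U* its mean on the rest. Then

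- full score: *F* = (1 − *p*)·*F_U* + *p*·*F_T*
- with minus without tagged items: *F* − *F_U* = *p*·(*F_T* − *F_U*)

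Neither *p* nor the two means can be taken from the article. The formula still shows two things. First, the level of the score moves whenever *p* and the gap are both non-zero. Second, if the gap were the same at all six sites, every score would shift equally and the slope of a linear association with outcomes would not change. The association is distorted only if the gap varies between sites, and nothing in the article shows that it does.

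**5. Where the questionnaire enters.** Stage 2 calculates component scores from component information and uses context to identify enablers and barriers. The abstract is looser: it names the questionnaire and the routine phase 1 data together as sources for both context and scores. On the more specific text, a respondent's absence in phase 1 affects mainly the explanation of the scores.

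**The case against.** The strongest reply is that documenting a model is not devising it. The article equates the model of care with the intervention, and that is the intervention delivered in phase 1 of a trial with its own cited publication. The phase 3 text may be a faithful record and the May 2015 changes may be clarifications. The per-protocol wording may be the missing anchor. A condensed article also need not print every step of its derivation.

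Much of this stands. A reader might infer that fidelity is not measured against phase 1 intent at all, or that components were added afterwards. The text does not support either: it reports changes to description, not additions, and the trial protocol that would show a departure is not at hand. A reader might also infer that the questionnaire has no tie to phase 1. That is wrong too: Methods/design says it is to describe the setting in which the study took place, and Stage 1 directs it at the structures supporting the intervention. Nor is it stated that the respondent will be the present manager rather than the phase 1 post-holder. Finally, one might infer that the error differs by site, but a single description applies to all six.

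What the reply does not remove is the stated sequence. The article chose to say when its reference was written and that it was changed, and so put a later, altered description in the place where its own definition requires the phase 1 intention. Questioning that choice is not a request for detail that belongs in a fuller document.

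**Conclusion.** The concern holds in limited form. Fidelity to phase 1 is to be scored against a description documented in phase 3 and modified in May 2015, with criteria and weights still open, no stated check against the phase 1 specification, and an unnamed protocol behind the per-protocol rule. The match to phase 1 intent is therefore not assured, and the score may mix non-delivery with later redefinition. It is not shown that the match is absent.

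No magnitude can be given. It depends on the weight share of changed items and on how differently sites scored on them, and any figure would only restate assumed values for both. The conclusion rests on phase 3 being later than phase 1 and on the modifications possibly being substantive; if they were purely editorial, the tagged and untagged results would show it. The questionnaire point is secondary and bears mainly on interpretation. The matter should be addressed because it concerns the main exposure variable and scoring is still described as future work.

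**What to change.** - Score the primary fidelity measure against the components as specified in the phase 1 trial protocol, and name that document where the per-protocol rule is stated.
- Tag each component description or measure that was added or modified after phase 1, including any compliance criteria added at the coming workshop.
- Report each community's score with and without the tagged items. If the two agree, the question is closed; if not, the reader sees how much rests on later wording.
- State phase 1 as the questionnaire's reference period, record whether each respondent was in post then, and use the planned follow-up interview to confirm this.

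The cost is the tagging, one more column in the planned score tables and a few lines on the questionnaire. Some phase 1 managers may not be reachable; recording who was in post at least makes that limitation visible.

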#### Describing the context for primary health care service delivery

A systematic literature review will be completed to identify the features of health services for Indigenous communities that contribute to effective primary health care interventions. The results will be used to develop a questionnaire to collect information about the health service context in the six intervention sites of the GBACC study. The objective of the questionnaire is to understand the management and service delivery support structures in place to support the intervention.

### Stage 2 – Assessment of implementation fidelity

The Stage 2 objective is to collect and analyse information about the service context and implementation of the model components. Information about model components will be used to calculate implementation fidelity scores for each component. Service context information will be analysed to identify enablers and barriers to implementation of components.

